## Abstract

Background: We aim to evaluate the effect of the Nordic Walking program on the quality of life and functionality of individuals with intellectual disabilities; Methods: The NORDIN-JOY study is designed as a multicenter, randomized crossover trial. Participants in the experimental group will engage in a Nordic Walking intervention, while those in the control group will participate in a Fit 5-Fitness Cards intervention. Both physical training programs will consist of two 60 min sessions per week over a three-month period. The study will assess measures of quality of life and physical fitness. Additionally, the feasibility and cost-effectiveness of both programs, as well as the average weekly physical activity levels during the six months following the intervention, will be evaluated; Results: The results of this study are anticipated to provide valuable insights into the effects of structured exercise interventions on individuals with intellectual disabilities. These findings will be disseminated through peer-reviewed journals and academic conferences; Conclusions: This protocol seeks to establish evidence on the impact of exercise programs in individuals with intellectual disabilities. The findings have the potential to inform specific recommendations for healthcare professionals, caregivers, and policymakers, promoting physical activity as a cost-effective strategy for improving care and quality of life in this population.

## 1. Introduction

According to data from the 2019 Global Burden of Disease study, an estimated 107.62 million individuals worldwide (1.74% of the population) have an intellectual disability (ID) [1].

Multiple factors shape the strategic planning of care for this population. Notably, the rising life expectancy, projected to reach 69.7 years in these nations [2], necessitates the provision of sustained and appropriate support systems throughout the lifespan, particularly for adults with ID who may outlive their primary caregivers [3]. On the other hand, premature aging, typically beginning around the age of 45, is associated with an increased prevalence of chronic conditions, such as chronic constipation, thyroid disorders, and obesity, often linked to sedentary behavior [4]. Notably, adults with ID experience functional decline as early as the fourth decade of their life, as a consequence of premature aging, as well as early signs of cognitive decline [5].

According to age-standardized mortality ratio data, 31.7% of recorded deaths among individuals with IDs were deemed avoidable, with 21.1% classified as treatable and 19.9% as preventable. These findings highlight the urgent need for targeted preventive strategies within this population [6]. In this regard, physical activity emerges as a key strategy for enhancing quality of life (QoL) and health, promoting active and healthy aging [7]. Engaging in physical activity provides numerous benefits for individuals with ID, including improved cardiorespiratory fitness, increased muscular strength, healthy weight management, and a reduced risk of high blood pressure, excessive weight gain, stroke, and elevated blood sugar levels [8].

In addition to this, it should be noted that physical fitness (PF) has been found to be predictive of a decline in daily function in the general population and in older adults with ID [9]. In accordance with this, it seems important to develop strategies aimed at improving health-related PF, which is a well-known marker of health that is considered to be an important predictor of morbidity and mortality for cardiovascular disease and for all causes [10]. Traditionally, body composition, cardiorespiratory and muscular fitness and flexibility, are considered the main components of health-related PF [11]. In this context, it is essential for both public and private authorities to develop prevention strategies centered on the promotion of physical activity, which is key to improving PF in individuals with ID. Such strategies should be designed to overcome common exercise barriers reported by individuals with ID, including economic cost, transportation issues, and lack of facilities [12]. Additionally, since exercise barriers may vary depending on the severity of ID, it is essential to promote activities that are motivating, enjoyable, and easy to perform [13].

Nordic Walking (NW) is proposed as an effective therapeutic approach, as walking is the most common form of exercise within this population [14]. The ability to walk is closely linked to daily physical fitness, cardiovascular health, and long-term independence. NW could serve as a valuable therapeutic intervention for this population for several reasons. Firstly, NW is regarded as a simple and feasible form of physical activity that can be performed by almost anyone, at any time, and in nearly any location [15]. Secondly, NW has been shown to have beneficial physical and psychological effects, including improvements in QoL [16]. Lastly, NW can be performed alongside family members and friends, enabling group exercise, which is likely to enhance adherence to this form of physical activity [17].

To enhance exercise adherence, it is essential to identify activities that provide a clear and motivating structure. In this sense, the Fit 5-Fitness Cards program seems to be an interesting option. This program was created with the aim of promoting regular physical activity, nutrition and hydration among Special Olympic athletes. The Fitness Cards program provides a comprehensive set of exercises targeting four key fitness components: endurance, strength, flexibility, and balance. These exercises are structured across multiple levels, allowing individuals to progress at their own pace and adapt routines to their specific abilities [18]. This approach facilitates the involvement of both participants and their caregivers, fostering autonomy and promoting a healthier lifestyle. Previous research has demonstrated that the Fit 5-Fitness program is an effective and appealing intervention, yielding significant improvements in various health metrics, including reductions in blood pressure and resting heart rate [19]. Furthermore, both the Fit 5-Fitness Cards program and NW could positively contribute to reducing obesity in individuals with ID [19,20]. These findings are particularly critical given the high prevalence of obesity in individuals with ID and the pressing need for multifactorial strategies that encourage physical activity to mitigate this issue.

Despite the interest in physical activity approaches, there remains a gap in research regarding their effectiveness in enhancing functionality and QoL among individuals with ID. While scientific literature has confirmed the benefits of NW in various populations, such as healthy older adults [21], and individuals with metabolic pathologies [22], studies on its potential impact on ID are scarce. To the best of the authors’ knowledge, existing research has primarily focused on body composition, balance and gait parameters in individuals with Down syndrome [23,24]. The only known study examining the effects of NW in this population assessed its impact on body composition and physical fitness in 12 obese women with ID [25]. Therefore, further research is needed to explore the broader benefits of NW for individuals with ID.

Regarding the Fit 5-Fitness Cards, the limited existing research has demonstrated their effectiveness in improving body composition and metabolic health among Special Olympic athletes [19]. However, only one study appears to have been conducted specifically with individuals with ID. In the study by Ptomey et al. [26], the Fit 5-Fitness Cards were utilized to promote physical activity among adults with ID as part of a comprehensive weight management intervention. This highlights the clear need for further research to evaluate the efficacy of this strategy in individuals with ID.

Therefore, the primary objective of this study is to evaluate the effect of the NW program on the QoL and functionality of individuals with ID. Additionally, the secondary objectives include assessing the impact of the Fit 5-Fitness Cards program on QoL and functionality, as well as comparing the safety, feasibility, and adherence of these two alternative exercise interventions.

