## 4. Discussion

People with ID have been shown to have low levels of physical activity practice [43]. In this regard, the performance of physical exercise among this population is considered a useful strategy, due to the positive impact that it has on their health [7]. Therefore, the primary objective of this study is to evaluate the effect of the NW program on the QoL and functionality of individuals with ID. Additionally, the secondary objectives include assessing the impact of the Fit 5-Fitness Cards program on QoL and functionality, as well as comparing the safety, feasibility, and adherence of these two alternative exercise interventions.

The expected results of this research are that NW will improve fitness and QoL among adults with ID. These findings have important policy implications. Policymakers should integrate NW into health promotion initiatives, allocate funding for accessible programs, and incorporate it into disability services and rehabilitation efforts. Training for caregivers and professionals should be prioritized to ensure safe implementation, while urban planning should support accessible walking paths. Embedding NW into public health policies can promote inclusivity and improve the well-being of individuals with disabilities.

In this context, it should be acknowledged that implementing NW programs requires tailored approaches to accommodate different ability levels. Disability service providers and community organizations should offer structured sessions, with trained caregivers and professionals to ensure safety and engagement. Adaptive techniques, individualized pacing, and social participation should be emphasized to maximize benefits. By following these recommendations, practitioners can enhance the overall health and QoL of adults with ID.

Previous studies have demonstrated that exercise interventions can effectively improve the QoL [44] and physical fitness [44,45,46] of an individual with ID. However, significant uncertainty remains regarding the effects of NW and the Fit 5-Fitness Cards program. The available evidence has primarily focused on a narrow range of outcomes, which may hinder the effective application of these findings in clinical settings. Therefore, it is essential to provide a comprehensive synthesis and evaluation of the current evidence.

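### The primary objective is Nordic Walking's own effect on QoL and functionality, but the design identifies only Nordic Walking relative to Fit 5, a contrast that no objective names for those outcomes

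*Protocol article*

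**What the plan says.** **Objectives.** The Introduction says that "the primary objective of this study is to evaluate the effect of the NW program on the QoL and functionality of individuals with ID", and Section 4 repeats the sentence. The secondary objectives also begin without a comparator: "the secondary objectives include assessing the impact of the Fit 5-Fitness Cards program on QoL and functionality". The one comparative objective is "comparing the safety, feasibility, and adherence of these two alternative exercise interventions". QoL and functionality are not in that list.

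**Design.** The Abstract says that "those in the control group will participate in a Fit 5-Fitness Cards intervention" and gives both programmes the same schedule: "Both physical training programs will consist of two 60 min sessions per week over a three-month period". Under Sections 2.1, 2.3 and 2.5, centres are randomised to NW then Fit 5, or the reverse, with a one-month washout between. No sequence is left without exercise. Section 2.4.5 schedules assessments before (T0) and after (T1) the first programme, one month later (T2), after the second programme (T3), and six months after that (T4).

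**Analysis.** Section 2.6 plans an inter-group test that includes a primary outcome, in the singular. Section 2.4.4 refers to primary outcomes in the plural. Neither section names one. Section 2.4.4 defines a cost-effectiveness ratio (CER) on each programme's pre-post change and an incremental ratio (ICER) of NW against Fit 5.

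**Expected conclusion.** Section 4 states: "The expected results of this research are that NW will improve fitness and QoL among adults with ID". It goes on to recommend that policymakers fund NW and build it into services.

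**The concern.** The objective asks whether NW works. The design asks whether NW works better or worse than another exercise programme of the same schedule, one that the Introduction itself describes as effective. The two questions can have different answers.

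If the objective is taken literally, the reported result would be a pre-post gain under NW, and a reader could take it as proof of benefit. The conditions for a spurious gain are present. Staff and participants are unblinded (Section 2.4). A family member or caregiver completes the QoL scale (Section 2.4.1). The people who run the exercise programme also administer the tests and the questionnaire (Section 2.4.5).

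If the planned between-programme test is reported instead, a null result would say nothing about NW's own effect. Either way, the policy recommendations in Section 4 need an absolute claim that the design cannot deliver.

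**Working it through.** **1. What randomisation identifies.** Let N and F be the true effects of NW and Fit 5 over a three-month programme. Let p1 and p2 be everything else that moves scores in periods 1 and 2: time, practice on the tests, regression to the mean, expectation. Assume no carryover. The expected pre-post changes are:

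| | Period 1 (T0 to T1) | Period 2 (T2 to T3) |
|---|---|---|
| Group A (NW first) | p1 + N | p2 + F |
| Group B (Fit 5 first) | p1 + F | p2 + N |

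- Between programmes: ½[(p1 + N) − (p1 + F)] + ½[(p2 + N) − (p2 + F)] = N − F. The period terms cancel.
- NW before-after change, averaged over groups: ½[(p1 + N) + (p2 + N)] = N + ½(p1 + p2). They do not cancel.

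Adding any constant c to N and F and subtracting it from p1 and p2 leaves all four cells unchanged. The data therefore cannot separate N from the drift, whatever the sample size. If N − F = 0, then N = F = 0 and N = F = 0.5 SD fit equally well.

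**2. Whether the washout supplies the missing control.** The T1 to T2 change is measured off programme. It is not randomised against anything, lasts one month rather than three, and follows three months of exercise, so it mixes drift with loss of the first programme's effect. It does not give p1 or p2.

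**3. Objectives set beside the planned contrasts.**

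| Outcome | Objective | Planned contrast |
|---|---|---|
| QoL, functionality | NW alone (primary); Fit 5 alone (secondary) | Inter-group test (2.6); ICER of NW against Fit 5, CER per programme (2.4.4) |
| Safety, feasibility, adherence | NW versus Fit 5 (secondary) | Consistent with the objective |

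The first row does not match. Section 4 adds to this by leaving to future studies the comparison of NW with other physical activities on fitness and QoL, which is the efficacy contrast that this trial randomises.

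**4. Whether the sample size settles the contrast.** Section 2.2 gives 67 participants from a Wilcoxon signed-rank test with d = 0.5, alpha 0.05 and power 0.80. It does not say whether the pair is before/after or NW/Fit 5.

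- Signed-rank test, two-sided, normal data: (1.960 + 0.842)² / 0.5² = 31.4. Dividing by the efficiency 3/π = 0.955 gives 32.9; the noncentral-t calculation gives 35 (39 under the minimum-efficiency assumption).
- Two-group Mann–Whitney test: 2 × 31.4 / 0.955 = 65.8 per group; the noncentral-t calculation gives 67 per group, 134 in total.

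The stated 67 does not follow from the named paired test and equals one arm of an unpaired comparison. That discrepancy is a separate matter. Here it shows only that the sample-size paragraph does not reveal which contrast was intended.

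**The case against.** The strongest reply is that the trial is comparative in everything but one sentence. The Abstract calls Fit 5 the control, Section 2.1 presents the crossover as a within-subject comparison, Section 2.2 says the design permits comparing the interventions, Section 2.4.4 defines an ICER of NW against Fit 5, and Section 2.6 tests the primary outcome between groups. Section 2.1 also calls the study a pilot, and Section 4 describes expected results only.

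Much of this stands, and it rules out some stronger readings:

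- A reader might infer that the protocol has committed to answering its primary objective by a before-after change. No section says so. The explicit pre-post quantity is the one in the CER.
- A reader might infer that comparing the programmes is no objective at all. It is one, for safety, feasibility and adherence.
- A reader might infer that there is no measured time off exercise. There is the washout, though it is not a usable control.
- A reader might count eight QoL domains and three functionality measures as separate primary tests and calculate an inflated error rate. The article does not say that the domains are tested separately, cites an average QoL score as an example in Section 2.4.4, and mentions a Bonferroni correction in Section 2.6, although of unclear scope. That count is not in the document.

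The reply does not remove the mismatch. The non-comparative objective appears twice, the expected result and the policy advice follow it, and the stated limitations do not mention the lack of an unexercised control. This is not detail left to an analysis plan: no analysis plan can make these two sequences estimate NW's absolute effect without bias.

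**Conclusion.** The point holds as a mismatch. The primary objective is non-comparative, the randomised design and the planned tests are comparative, and the contrast that randomisation supports on QoL and functionality is named in no objective. The primary outcome is also unnamed and is referred to in both singular and plural.

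The bias in a before-after estimate of NW's effect is the average drift over the two periods, added in full. The article gives nothing from which to estimate it, so no figure is offered. The result in the working assumes no carryover; carryover would complicate the NW versus Fit 5 contrast but would not make NW's own effect estimable. How precisely four centres can estimate NW minus Fit 5 is a different question.

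This should be corrected before results are interpreted. It does not invalidate the trial, which can still answer the comparative question.

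**What to change.** 1. In the Introduction and Section 4, state the primary objective and hypothesis as the within-participant difference between NW and Fit 5 at end of period (T1 and T3) in one named outcome. If that outcome is QoL, define the summary score, since Section 2.4.1 describes only items and domains.
2. Make the other QoL and functionality measures secondary, and use the same single primary outcome in Sections 2.4.4 and 2.6. Direct the primary analysis in Section 2.6 at this within-participant contrast.
3. Label pre-post changes within each programme, including the change in the CER, as descriptive and uncontrolled.
4. In Section 2.2, say that d = 0.5 refers to NW versus Fit 5, and justify it for two active programmes of equal schedule.
5. Limit the conclusions and policy statements in Section 4 to NW relative to Fit 5, and add the missing unexercised control to the limitations.

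These are changes of wording and specification, with no new measurements or participants. The costs are a narrower claim and, if d = 0.5 cannot be defended for this contrast, a fresh look at the sample size.

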## 2. Materials and Methods

### 2.1. Study Design

This is a pilot study employing a crossover, cluster-randomized design with repeated measures. This design allows for a within-subject comparison, reducing inter-individual variability and increasing statistical efficiency compared to parallel-group trials, where each subject receives only one treatment [27]. Participating centers will be randomized in a 1:1 ratio into two groups. Two sequential interventions (NW program and Fit 5-Fitness Cards) will be conducted, separated by a 4-week washout period to mitigate potential carryover effects [27]. Following the washout period, the interventions will be repeated in reverse order, adhering strictly to the established protocol. A comprehensive outline of the design and procedures is presented in Figure 1.

### 2.2. Participants

The sample size was estimated using G*Power (version 3.1., University of Düsseldorf, City, Germany) [28]. A priori power analysis, based on the Wilcoxon signed-rank test, was conducted with an alpha level of 0.05, statistical power of 0.80, and a moderate effect size (Cohen’s d = 0.5). The analysis determined that 67 participants were required. To account for potential dropouts, the final sample size was set at 100 participants, with recruitment evenly distributed across four centers (approximately 25 participants per center). This design ensures robust data collection while allowing for comparative analysis of the interventions.

Participants for this study will be recruited through invitation letters distributed via four associations located across Spain. Eligibility criteria for inclusion in the study are as follows: (a) a confirmed diagnosis of ID arising from neurodevelopmental disorders or autism spectrum disorders; (b) classification of moderate or mild ID (based on a combination of IQ (Intellectual Quotient) scores and adaptive behavior), as defined by the criteria of the Spanish National Health System; and (c) Independent ambulatory ability.

The legal representatives or caregivers of potential participants will be responsible for consulting with the individuals, regarding their willingness to participate in the study and providing written consent on their behalf. Additionally, all participants will have the opportunity to express their own consent or assent regarding their involvement [29].

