### 2.6. Statistical Analysis

Data will be reported as medians and interquartile ranges for non-normally distributed variables (checked with the Kolmogorov-Smirnoff test) or as means and standard deviations for normally distributed variables. Qualitative variables will be reported as n (%). The intra-cluster correlation coefficient and the cluster-specific effects will also be calculated. Inter-group quantitative variables will be compared, including the primary outcome, with an unpaired, two-tailed t test or the Mann–Whitney U test, as applicable. For inter-group dichotomous data comparison, the two-tailed chi-square tests will be used, with the Yates correction or Fisher’s exact test as appropriate. For repeated measures analysis, the two-way analysis of variance with the Bonferroni correction or the Friedman test, as appropriate, will be used. Comparison will be adjusted by cluster effect. Subgroup analysis of the primary outcome will include sex, age, BMI (normal, overweight and obese), level of physical activity (Inactive, Active), and level of ID (mild, moderate, severe). Multivariate regression models will adjust for confounders such as sex, age, BMI, physical activity, and ID level. Multicollinearity will be checked using the Variance Inflation Factor (VIF), with VIF > 5 indicating high collinearity [42]. Sensitivity analyses will assess robustness. Statistical significance will be set at a two-tailed *p*-value of less than 0.05. All analyses will be conducted using SPSS v24.0 software (IBM Corp., Armonk, NY, USA).

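### The stated 67 participants does not follow from the signed-rank calculation in section 2.2, whose inputs give 35

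*Protocol article*

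**What the plan says.** Protocol article, section 2.2 (Participants), names the software, "The sample size was estimated using G*Power (version 3.1", and then the test and its error rates: "A priori power analysis, based on the Wilcoxon signed-rank test, was conducted with an alpha level of 0.05, statistical power of 0.80". The effect size is a Cohen's d of 0.5, called moderate. The result is "The analysis determined that 67 participants were required", raised to 100 for dropout and spread over four centres at about 25 each. The section gives neither the sidedness of the test nor the assumed parent distribution. It also does not say whether d is standardised by the SD of within-person differences or of raw scores.

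Section 2.1 (Study Design) describes a cluster-randomised crossover in which every participant receives both programmes, and justifies it by the efficiency of within-subject comparison. Section 2.6 (Statistical Analysis) sets two-tailed significance and states: "Inter-group quantitative variables will be compared, including the primary outcome, with an unpaired, two-tailed t test", with Mann-Whitney as the alternative. It also lists repeated-measures analyses and an adjustment for cluster.

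**The concern.** The protocol prints both the inputs and the output of its sample size calculation, so a reader can check one against the other. They disagree by a factor of nearly two (67 / 35 = 1.91). The test used for planning is paired, while the test that section 2.6 ties by name to the primary outcome is unpaired. A reader therefore cannot tell which analysis the 80% power claim describes, what effect size it refers to, or whether 67 counts people in total or per group. The dropout allowance inherits the problem, because going from 67 to 100 treats 67 completers as the number that secures the stated power.

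**Working it through.** **Inputs.** From section 2.2: signed-rank test, alpha 0.05, power 0.80, d = 0.5. From section 2.6: two-tailed testing, which section 2.2 does not state, so one-sided results are shown as well. Assumed, because not given: the parent distribution (all usual options tried) and d as the standardised within-person difference (relaxed in step 4).

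**Method.** The asymptotic relative efficiency (ARE) approach, of the kind G*Power uses for Wilcoxon tests. The sample size n is multiplied by the ARE and entered in a noncentral t calculation.
- Signed-rank: df = n × ARE − 1; noncentrality = d × √(n × ARE).
- Mann-Whitney, n per group: df = 2 × n × ARE − 2; noncentrality = d × √(n × ARE / 2).
- ARE: normal 3/π = 0.955; minimum 0.864; logistic π²/9 = 1.097; Laplace 1.5.

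**Step 1: try to reproduce 67 with the named test.** Two-sided, normal parent:
- n = 34: n × ARE = 32.47, noncentrality 0.5 × √32.47 = 2.849, power 0.788.
- n = 35: n × ARE = 33.42, noncentrality 0.5 × √33.42 = 2.891, power 0.801.

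So 35 are required. A simulation of the signed-rank test on normal data (3,000 runs) gave 80.1% power at n = 35. The other options, at power 0.80:

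| Parent | Two-sided | One-sided |
|---|---|---|
| Normal | 35 | 28 |
| Minimum ARE | 39 | 31 |
| Logistic | 31 | 24 |
| Laplace | 23 | 18 |

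None is near 67. Even with power raised to 0.95, the largest two-sided figure is 63.

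**Step 2: what 67 delivers with the named test.** Two-sided, normal parent: n × ARE = 63.98, noncentrality 0.5 × √63.98 = 3.999, power 0.976 (simulation 0.978). Setting power to 0.80 instead and solving for d gives d = 0.356.

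**Step 3: a calculation that does return 67.** Two-sided Mann-Whitney, normal parent, d = 0.5:
- 66 per group: power 0.795.
- 67 per group: df = 2 × 63.98 − 2 = 125.96, noncentrality 0.5 × √(63.98 / 2) = 2.828, power 0.801.

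The match is exact, at 67 per group or 2 × 67 = 134 in two separate groups.

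**Step 4: the effect of how d is defined.** If 0.5 is standardised by the raw-score SD and r is the within-person correlation, the paired effect is dz = 0.5 / √(2(1 − r)). Two-sided signed-rank, normal parent:

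| r | dz | n |
|---|---|---|
| 0 | 0.354 | 68 |
| 0.1 | 0.373 | 62 |
| 0.25 | 0.408 | 52 |
| 0.5 | 0.500 | 35 |
| 0.7 | 0.645 | 22 |

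Only r = 0 comes close, and it gives 68 rather than 67.

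**Step 5: the unpaired test of section 2.6.** The result depends on which observations are compared, and section 2.6 does not say.
- *Raw scores between the two sequence groups in a single period:* 67 people in total (33 or 34 per group) give power 0.50 to 0.51; 100 in total (50 per group) give 0.68; 134 in total give 0.80.
- *Both periods, Nordic Walking scores against Fit 5 scores:* 67 completers supply 67 observations per condition. Simulated Mann-Whitney power at a raw-score d of 0.5 is about 79% at within-person correlation 0, 84% at 0.3, 88% at 0.5 and 93% at 0.7, ignoring period, carryover and cluster effects.

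**The case against.** The strongest reply is that the error is harmless or conservative. For the test that section 2.2 names, 67 is nearly twice what is needed, enrolment is set at 100, and the study is labelled a pilot. This stands as far as it goes: nothing here shows a shortfall for a paired analysis before clustering. It does not make the printed figure right, and the protocol itself chose to claim 80% power.

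A second reply is that 67 could come from a raw-score d with zero within-person correlation. Section 2.2 states no correlation, zero would undercut the within-subject efficiency argued in section 2.1, and the result is 68. The reply does show that 35 depends on the reading of d, so that condition has to be attached to it.

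A reader might go further and infer that 67 is a misreported per-group number, so that the trial needs 134 people and has only 50% to 68% power. The documents do not support this. The Mann-Whitney origin is inferred from a numerical match and stated nowhere. The low power figures require a raw-score comparison between sequence groups in one period, which section 2.6 does not specify. The article also uses the word group for the interventions (section 2.4.4, for instance, on cost-effectiveness), so an unpaired comparison of the two conditions over both periods is an equally available reading, and 67 completers then give roughly 80% power or more. Section 2.6 also plans repeated-measures analyses.

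**Conclusion.** Wrong as written, and it should be corrected, but as an error in the planning statement and not as evidence of an underpowered trial. The stated inputs give 35 participants, not 67 (range 18 to 39 over all parent distributions and both sidedness options). This takes d as the standardised within-person difference and participants as independent. On the same assumptions, with a two-sided test and a normal parent, 67 completers give about 98% power at d = 0.5. Clustering by centre, which the calculation does not mention, would change these figures; it is a separate matter and does not explain the 67. The arithmetic mismatch is certain, its origin is not, and the power of the unpaired comparison cannot be settled until section 2.6 says which observations it uses.

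**What to change.** In section 2.2, rerun the calculation for the test that will be used on the primary outcome, and align it with section 2.6. State:
- the test, its sidedness and the parent distribution assumed;
- whether d is standardised by the SD of within-person differences or of raw scores, with the assumed correlation in the latter case;
- whether the resulting number is a total or per group;
- the power or detectable effect that follows, with enrolment kept at 100.

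If the primary analysis is paired, the text would read 35 required, or d of about 0.36 detectable at 80% power with 67 completers, both before clustering. If it is unpaired, say whether one period or both are used before quoting any power. The 50%, 68% and 134 figures belong in the text only for a single-period raw-score comparison between sequence groups.

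The cost is a few sentences in section 2.2 and a clarifying phrase in section 2.6, with no change in enrolment.
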